**Family participants**

Baseline and follow-up data will be collected by self-completion questionnaire. Baseline questionnaires will be given to family participants when they attend Children’s Centres by the researchers from each of the four study coordinating centres or by the relevant Children’s Centre staff, or will be posted by Children’s Centre staff. Questionnaires can be self-completed whilst at the Children’s Centre and handed to researchers or Children’s Centre staff, taken home and completed, or completed wherever the parents prefer and returned to researchers using freepost envelopes. One reminder will be sent to any parent who does not return the questionnaire. Follow-up data and the reminder, if necessary, will be collected by postal, telephone, home visit, or at Children’s Centres, which ever method is preferred by the participant. If necessary, a home visit will be undertaken to help completion of a questionnaire. Mode of administration will be recorded. Data will be entered onto identical databases at each study coordinating centre and stored on NHS or University servers. Once data collection is completed, data will be merged onto one database prior to analysis. At the end of the trial, data from all centres will be archived by the Nottingham centre for a period of seven years as set out in the University of Nottingham’s Code of Research Conduct.

The questionnaires are in the process of being developed and will be sent to the REC prior to being used within the study. Questionnaires will include questions on socio-demographic information about the household, previous fire-related accidents, fire safety behaviours and fire-safety equipment, knowledge and understanding of what causes fires, home safety information provided by Children’s Centres and their perception of the effectiveness of this information. The follow –up questionnaire will be identical to the baseline questionnaire except it will not collect socio-demographic data and it will collect data about resource-use and expenditure incurred as a result of the intervention; i.e. travel costs to attend educational sessions, equipment purchased and services attended. (e.g. smoking cessation). Parents returning completed questionnaires will be sent £5 gift vouchers for use in local stores as previous systematic reviews show small monetary incentives increase response rates^15^. Questionnaires will be developed and piloted with families between January – April 2011.

**Children’s Centres as participants**

Data will be collected on the proportion of Children’s Centres providing information and advice on the prevention of fire-related injury. This will include fire escape planning, smoke alarms, preventing fire-setting or match play, use of bedtime routines for preventing fires, smoking cessation and referral to smoking cessation services. These data will be collected from Children’s Centre managers, in all trial arms, via postal, telephone or email questionnaire at baseline and at 12 months post commencement of the intervention in the IPB plus facilitation (I_1_) and the IPB without facilitation (I_2_) arms and at 12 months post randomisation in the control arm. Mode of administration will be recorded. Questionnaires will be developed and piloted with Children’s Centres managers between January – April 2011.

Children’s Centre managers and staff in the IPB plus facilitation (I_1_) and the IPB without facilitation (I_2_) arms will have telephone and face-face contact with the research team to explore the success of implementing the IPB at months 1, 3, 4-5 and 8 (see page 22 for details). Implementation successes and difficulties will be recorded at each contact.

Children’s Centre managers and staff in the IPB plus facilitation (I_1_) and the IPB without facilitation (I_2_) arms will also be asked to complete a paper-based implementation measurement tool (which will be developed between Jan – April 2001 and will be based on The PARIHS (Promoting Action on Research in Health Services)^16^ framework to explore the success of the implementation process. This will take place at the end of the 12 month intervention period. The PARIHS framework is an evaluation instrument to explore the effectiveness of implementation strategies. This includes three core elements that determine the success of research implementation in each of which there are several components:

1. Evidence – the strength and nature of the evidence as perceived by multiple stakeholders. The four components relate to the different sources of evidence.
2. Context – the quality of the context or environment in which the research is implemented. The three components relate to the organisational culture, leadership and the organisations evaluation.
3. Facilitation – processes by which implementation is facilitated. The three components relate to facilitation, firstly as enabling, secondly as responsive and interactive, and thirdly as internal or external.

At the end of the 12 month intervention period, information about the barriers and facilitators to implementing the intervention will be collected using a nested qualitative study. This is an important aspect to the trial to be able to explore the process of implementing the intervention, how the study and the intervention fit into the context of Children’s Centres, the unmet needs of the Children’s Centre managers and staff, levels of adherence to the intervention and for whom the intervention appeared to work best, This will be in the form of semi-structured interviews (telephone or face-to-face) of Children’s Centre managers and/or staff responsible for the delivery of the IPB in the IPB plus facilitation (I_1_) and the IPB without facilitation (I_2_) arms. We will use a purposive sample of Centres in the two intervention arms in each study area (maximum of 18 interviews). This will allow us to get a range based on various characteristics including implementation of the IPB, which will be assessed based on the telephone and face-face contacts with the research team (described on page 22) and the implementation measurement tool devised using the PARIHS framework^16^.

The interview guide will be developed using the results of the systematic review of the barriers and facilitators for home injury prevention interventions, the interviews that were undertaken with Children’s Centre managers and staff in earlier parts of the programme of research and the PARIHS framework. This will cover the following areas:

- Children’s Centre manager’s/staff’s overall perception of the intervention
- Who delivered the intervention eg. Children’s Centre staff, health visitor
- What were the barriers to implementing the intervention (covering the 3 core elements in the PARIHS framework)
- What were the facilitators to implementing the intervention (covering the 3 core elements in the PARIHS framework)
- The resources used to implement the intervention
- Other issues that the Children’s Centre manager/staff want to raise

Recording, transcribing and security of data

Consent forms and questionnaires will be treated as confidential documents and held securely at each study coordinating centre and all identifiable information will be removed once they are received. The interviews will be digitally audio-recorded with the consent of the participant and the participant will be identified only by their UIC. They will be anonymised and stored with the research data as source data. Audio-recordings will be transcribed verbatim. Data will be entered onto identical databases at each study coordinating centre and stored on password protected NHS or University servers. At the end of the trial, data from all centres will be archived by the Nottingham centre for a period of seven years as set out in the University of Nottingham’s Code of Research Conduct.

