## PRIMARY OBJECTIVE

To test the hypothesis that providing facilitation for delivering the fire-related injury IPB to Children’s Centres is more effective, and cost-effective, than providing the fire-related IPB without facilitation or than usual care in increasing the proportion of families attending Children’s Centre who have a fire escape plan. The primary objective relates to fire escape planning as there was evidence from the systematic reviews and decision analyses described above that interventions can be effective and cost effective in increasing fire escape planning by families. Although the best evidence exists for interventions to promote smoke alarm use, this was not chosen as the primary outcome measure due to the high prevalence of functioning smoke alarms (> 90%) found in the interviews with parents attending Children’s Centres in an earlier piece of work within the programme.

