### Secondary endpoint

Secondary outcome measures (also ascertained from self-completion questionnaire) will include:

1. The proportion of families with smoke alarms fitted and working on every level;
2. The proportion of families who report fire setting or match play by their children;
3. The proportion of families who have a bedtime routine for preventing fires;
4. The proportion of families who take part in smoking cessation courses/support;
5. Score for families’ knowledge of the causes of fires in the home;
6. The proportion of families who are satisfied with home safety information provided by Children’s Centre;
7. Families’ resource-use and expenditure in the I_1_ and I_2_ arms incurred as a result of the intervention.

Children’s Centres as participants

1. The proportion of Children’s Centres providing information and advice on the prevention of fire-related injury including: fire escape planning, smoke alarms, preventing fire-setting or match play, use of bedtime routines for preventing fires, smoking cessation and referral to smoking cessation services (ascertained from Children’s Centre self-completion questionnaire);
2. The identification of the barriers and facilitators to Children’s Centres implementing the IPB (only in Children’s Centres in the I_1_ and I_2_ arms) (ascertained from interviews with Children’s Centre managers/staff);
3. A comparison of the resource-use and expenditure incurred as a result of the intervention in the I_1_ and I_2_ arms (ascertained from Children’s Centre self-completion questionnaire);
4. The success of implementing the IPB in Children’s Centres (only in Children’s Centres in the I_1_ and I_2_ arms) (ascertained from self completion implementation measurement tool based on the PARIHS framework^16^ and telephone and face-face contacts with research team at months 1, 3, 4-5 and 8);
5. The demographic characteristics of those participating families compared with those in the catchment area of Children’s Centres (ascertained from baseline questionnaire from participating families and data routinely collected by Children’s Centres).

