## TRIAL TREATMENT AND REGIMEN

The intervention will include the provision of an IPB on fire-related injuries, and facilitation to implement the briefing. Any Centre allocated to the control arm, ‘usual care’, will continue to use health promotion guidelines if they are already using them. A schematic diagram of the trial and the IPB is attached to this protocol.

There are 3 arms to this RCT:

I_1_ = Provision of IPB and facilitation for delivering it;

I_2_ = Provision of IPB without facilitation;

C =Usual care.

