### Facilitation of the IPB and compliance with the intervention

A facilitation package will be designed to ensure as consistent an approach to facilitation within each intervention Children’s Centre as possible. Discussions will take place between each Fire & Rescue Service local to the four study coordinating centres about the IPB and its implementation. The package will comprise the following:

1. Training session run jointly between the local research team and the Fire & Rescue Service. This will be followed by a meeting run by the same team to design a plan for implementing the IPB in each Children’s Centre and Centres will be expected to provide at least one fire safety session for all parents taking part in the study.
2. One month follow-up telephone contact from the research team to monitor progress and answer any questions;
3. Three month face-to-face meeting between Children’s Centre and research team to monitor progress;
4. Additional meeting at 4-5 months if any Children’s Centre in a study coordinating centre is experiencing difficulties or problems in implementing the IPB;
5. Eight month follow-up telephone contact to monitor progress.

Each contact with a Children’s Centre will be recorded by each research team, together with relevant field notes, on a form and retained within the study notes in each study coordinating centre. Compliance with the intervention will be assessed from the telephone and face to face contacts.

Potential risks and burdens for research participants.

We do not anticipate any potential risks to study participants. The main burden for Children’s Centres will be the time taken to complete questionnaires, undertake the interview and the self-completion tools (see above for details). For family participants, the main obligation will be the time taken to complete the questionnaires (baseline and follow-up). For those families in the IPB with facilitation arm there will also be the time taken to attend between 1 - 5 fire safety sessions at the Children's Centre.

If any participants have suffered a house fire or has had relatives of friends injured in one this may cause distress when parents complete questionnaires. Researchers will be trained to respond sensitively in such situations for example when discussing the study with parents or helping them to complete questionnaires. Specific advice is given in the IPB for Children's Centres about undertaking fire safety sessions in such circumstances.

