**ANALYSES**

# Statistics

### Methods

An analysis plan will be produced by the trial statistician and health economist, who will oversee and/or undertake the statistical and economic analyses.

All analyses will be conducted on an intention-to-treat basis in that families and Children’s Centre managers and staff will be analysed in the group to which they were randomised, regardless of the intervention actually received (eg. if the family moved and used a different Children’s Centre). Analyses will conform to a pre-specified analysis plan and will be undertaken blind to treatment arm allocation.

Characteristics of Children’s Centres and families at baseline will be compared informally between the three treatment arms. The primary outcome measure (having a fire escape plan at 12 months) will be described using frequencies and percentages and compared between treatment arms (I_1_ vs C; I_2_ vs C and I_1_ vs I_2_) using random effects logistic regression to estimate odds ratios and 95% CI. This analysis will have families at level one and Children’s Centres at level two, to allow for clustering of responses within Children's Centres. The primary analysis will adjust for randomisation stratum (study coordinating centre) as a fixed effect and will also adjust for the lead agency of the Children's Centre (Local Authority or NHS led), having a fire escape plan at baseline and deprivation (measured using IMD2007 obtained from families’ postcode). Deprivation has been specified as it is strongly associated with house fire injuries^2,3^ and measures of deprivation have previously been found to be associated with the effectiveness of home injury prevention interventions^18^.

The ICC and 95% CI will be estimated for the primary outcome measure from the regression models. Models will be checked by examining level 2 residuals for normality and constant variance and level 1 and level 2 residuals for outliers.

Sub-group analyses will explore differential effects by deprivation, measured using the IMD2007, by adding interaction terms to the regression model for the primary outcome measure. IMD will be entered as a continuous covariate if there is a linear relationship with outcome.

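### The arm defined as the IPB without facilitation is scheduled for research-team contacts that the protocol elsewhere lists as facilitation, which can dilute I1 vs I2 by an unknown amount

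*Protocol*

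**What the plan says.** **What I2 is.** The protocol's Trial Treatment and Regimen section defines the second arm as "Provision of IPB without facilitation".

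**What I2 is scheduled for.** Under Data collection, Children's Centres as participants, managers and staff in I1 and "the IPB without facilitation (I_2_) arms will have telephone and face-face contact with the research team" to explore how implementation is going, "at months 1, 3, 4-5 and 8 (see page 22 for details". The Secondary endpoint section names the same source for implementation success in I1 and I2: "telephone and face-face contacts with research team at months 1, 3, 4-5 and 8". The paragraph on the qualitative study then relies on these contacts to choose interviewees in both arms.

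**What those contacts are.** The only description of their content is in Facilitation of the IPB and compliance with the intervention. There they form items 2 to 5 of a five-item facilitation package. Item 2 is "One month follow-up telephone contact from the research team to monitor progress and answer any questions". Item 4 is an additional meeting at 4-5 months where a Centre "is experiencing difficulties or problems in implementing the IPB".

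**What depends on it.** The primary hypothesis is that facilitation "is more effective, and cost-effective, than providing the fire-related IPB without facilitation or than usual care". The Methods section has the primary outcome "compared between treatment arms (I_1_ vs C; I_2_ vs C and I_1_ vs I_2".

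**The concern.** The trial is meant to separate two things: handing over the briefing, and helping Centres to use it. If the arm that should get only the briefing also has scheduled conversations in which the research team answers questions and meets Centres in difficulty, part of the help reaches both arms.

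Two of the three planned comparisons are affected.

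- **I1 vs I2:** shared support brings the arms closer together, so the expected bias is towards no difference.
- **I2 vs control:** control Centres are scheduled for questionnaires only. The comparison would therefore estimate the IPB plus research-team contact rather than the IPB alone.

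The cost comparison of I1 and I2 inherits the same doubt, because it is unclear which contacts count as the cost of facilitation.

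**Working it through.** **1. The schedules side by side**

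| Facilitation package item | Purpose given there | Scheduled for I2 in the data-collection section? |
|---|---|---|
| 1. Joint training with the Fire & Rescue Service, then a planning meeting for the Centre | Train staff, design the implementation plan, at least one fire safety session expected | No |
| 2. Month 1 telephone contact | Monitor progress, answer questions | Month matches |
| 3. Month 3 face-to-face meeting | Monitor progress | Month matches |
| 4. Month 4-5 meeting | Only if there are difficulties | Month matches |
| 5. Month 8 telephone contact | Monitor progress | Month matches |

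Four of the five items coincide with contacts scheduled for I2, and one of those four is conditional. This is a count of items, not a share of effect.

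**2. The cross-reference.** The data-collection section points to page 22. The contents list puts the facilitation heading on page 21 and the next heading, on terminating the trial, on page 22. The reference therefore apparently means the facilitation section. No other text describes contacts at these months, and none gives a measurement-only version for I2.

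**3. The stated sample size.** Inputs from Sample size and justification: 42% in control, a 20-point difference (so 62%), 80% power, two-sided 5%, ICC 0.05, 20 families per Centre.

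- Design effect = 1 + (20 − 1) × 0.05 = 1.95.
- Families per arm before clustering = [1.96 × √(2 × 0.52 × 0.48) + 0.8416 × √(0.42 × 0.58 + 0.62 × 0.38)]² / 0.20² = 97, or 107 with continuity correction.
- Centres per arm = 107 × 1.95 / 20 = 10.43, rounded up to 11.

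The stated 11 per arm is reproduced. It concerns I1 or I2 against control, so the protocol has no power figure for I1 vs I2 to correct.

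**4. Illustration of dilution.** Assumptions that the protocol does not give: I1 at 62%, I2 at 42% without contacts, and contacts that pass a fraction f of the gap to I2. Then I2 = 0.42 + f × 0.20. The effective number per arm is Centres × 20 / 1.95, which is 112.8 for 11 Centres and 123.1 for 12.

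Power = Φ{[d√n − 1.96 × √(2p̄(1 − p̄))] / √(p₁(1 − p₁) + p₂(1 − p₂))}, where d is the gap and p̄ the mean of the two proportions.

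| f | I2 | Gap (points) | Power, 11 Centres | Power, 12 Centres |
|---|---|---|---|---|
| 0 | 42% | 20 | 86% | 89% |
| 0.25 | 47% | 15 | 62% | 66% |
| 0.50 | 52% | 10 | 33% | 35% |
| 0.75 | 57% | 5 | 12% | 12% |

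Using the unpooled variance throughout, the 12-Centre figures for 20 and 10 points are 89% and 36%. A t-based calculation on the number of Centres gives 83% (11) and 86% (12) for the 20-point gap.

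**The case against.** The strongest reply is that the contacts are measurement. The data-collection section says they explore implementation and that successes and difficulties are recorded each time. The facilitation section says compliance is assessed from them. Observing both IPB arms on one schedule is a defensible choice, and nowhere does the protocol say outright that I2 receives the package. The attached schematic and the flowchart, not visible here, might set out contacts by arm.

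This stands in part. A measurement purpose is stated, and delivery of facilitation to I2 is what follows from reading the sections together, not an explicit instruction. It does not remove the contradiction. Where the content is described, it includes answering questions and meeting Centres in difficulty, which is support. The package text also speaks of intervention Centres generally, without limiting it to I1.

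A reader might infer from four items out of five that the I1 vs I2 contrast is largely removed. The documents do not support that. The training and the Centre-specific plan, with its expected fire safety session, are not scheduled for I2. The 1 to 5 fire safety sessions are mentioned as a burden only for families in the facilitation arm.

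The power figures are also open to challenge. A 20-point I1-I2 gap starting from 42% implies that the IPB alone does nothing. If I2 would reach 52% without any contacts, power with 11 Centres is already 33% before any dilution. The fall in the table is therefore not evidence of what the contacts would do.

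**Conclusion.** The contradiction is established from the text: I2 is defined as having no facilitation, yet is scheduled for contacts whose only description is as facilitation. Following the protocol as written gives I2 part of the package. This can bias a comparison in the primary hypothesis towards no difference and changes what I2 vs control estimates.

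The size of the bias is unknown. It depends on how much of any facilitation effect the contacts carry, which the protocol does not say. The power range of 86-89%, 33-36% and 12% for gaps of 20, 10 and 5 points rests on assumed proportions and shows sensitivity only.

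A reader might also infer that a null I1 vs I2 result could not be interpreted at all. That goes too far: contacts are documented with field notes, the implementation tool covers facilitation, interviews are planned in both arms, and the I1 vs control comparison is untouched. It does need settling before Centres start, since contacts already made cannot be withdrawn.

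**What to change.** Reconcile the Secondary endpoint section, both data-collection paragraphs that use the contacts (implementation contacts and interview sampling), the arm definitions and the facilitation section, so that they state by arm which contacts take place and what they contain.

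- **I1 only:** the supportive content, meaning answering questions, problem-solving and the extra meeting for Centres in difficulty.
- **I2:** any contact at months 1, 3, 4-5 and 8 is record-only, by a standard form or a one-way written return, with no advice or problem-solving.
- **Both arms:** use the end-of-period implementation tool, the 12-month manager questionnaire and the interviews as the common measures of implementation.

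The cost is protocol wording, a short form and brief instructions to the research teams. There is a real downside: in-period field notes from I2 will be less rich, which weakens the basis for choosing I2 interviewees, and in-period implementation data will be collected somewhat differently in the two arms. Removing I2 contacts altogether would make this worse, because it would drop the I2 half of a listed outcome source; a record-only contact keeps it.
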